##### Study Intervention

The intervention is administered by a trained MEI coach and includes substance use screening brief interventions and ongoing monitoring throughout the prevention and treatment care cascade [72]. Coaches begin in the initial face-to-face visit with building rapport, explaining the intervention, and identifying personal and health goals. Health goals focus on medication adherence, health care engagement and satisfaction, substance use, and sexual health. Coaches then map out and help the participant prioritize each goal. After the initial question-answer period and establishment of goals, the MEI coach develops an individually tailored plan that is designed to utilize self-determination theory [83] and the Integrated Theory of Health Behavior Change [84] to facilitate the adoption and maintenance of health behaviors. The approach is centered on identified participant goals and values and care engagement, utilizing a card-sort procedure to help prioritize participant goals for each session [77]. Participants who score positive on the CRAFFT (car, relax, alone, forget, friends, and trouble) and Alcohol, Smoking, and Substance Involvement Screening Test are provided with prevention psycho-education around substance use risks [72,73,85]. Participants who score 2 to 3 on the CRAFFT are encouraged to develop a change plan to reduce substance use and scheduled for additional intervention sessions. These cutoffs were used because a CRAFFT score of 2 or higher is optimal for identifying any substance-related problem and an SUD (according to the Diagnostic and Statistical Manual of Mental Disorders, 5th Edition criteria) [86]. Coaches subsequently attempt to link participants who score above 4 to substance use services. Participants who describe sexual risk (eg, condomless anal sex) are also provided psycho-education around sexual risk and PrEP. Coaches help participants develop strategies to avoid substance use and sexual risks in the future.

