Telephonic and app-based check-ins between the MEI coach and participants are conducted to maintain rapport, open communication, review progress on personally identified goals, help troubleshoot challenges that may arise, and provide reminders for upcoming face-to-face visits. The app is used to facilitate communication around medication adherence, medical visit completion, video chat, and bidirectional communication. The MEI coach will determine the participant’s desire for support, and the frequency and schedule of messages. It is the aspirational goal of the study to have the MEI coach have weekly contact with participants; however, this is often not realistic for all participants. For example, some participants will embrace weekly check-ins, others prefer to engage more intermittently, and the remaining participants may experience situational or motivational barriers that may interfere with engagement. MEI coaches may need to utilize MI strategies to explore readiness to engage in telephonic check-ins and study visits and troubleshoot barriers that may arise (Table 1), and re-engagement needs to be pursued by the MEI coach. MEI coaches seek to check-in with participants weekly (at a minimum), and participants are encouraged to attend face-to-face follow-up coach visits at 3, 6, and 12 months. During these face-to-face visits, coaches will work with the participant to review, motivate, and reinforce personal life events, health care engagement, review substance and risk reduction goals, and problem-solve. Using this MI approach, the participant is thus empowered to take the lead with recommendations and guidance from the MEI coach. Permission is sought to audio-record each initial and follow-up study visit for the purpose of assessing study fidelity and providing routine, ongoing feedback to the MEI coach. The recording is at the discretion and informed consent of the participant and the MEI coach. Ad hoc telephonic and in-person support is also provided by the MEI coach, as requested by the participant. An MEI coach, at any time may help, for example, with referral to behavioral health, job resources, community support resources (eg, a food bank), provide supportive listing, or help arrange any requested sexually transmitted infection testing.

**Table 1 table1:** Motivational interviewing approaches to address level of interest in telephonic engagement.

Participant comments	Stage of change	MEI^a^ coach approach

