#### Sample Size Considerations

We aim to recruit up to 2000 YBLMSM and YBLTW to be screened for eligibility for aims 2 and 3. We conservatively estimate that 15.00% of the RDS recruited sample will be HIV-infected and not virally suppressed, given an HIV prevalence of 25% to 40% among YBLMSM and YBLTW across the sites and as many as 60% of HIV-infected YBLMSM are undiagnosed [4,9].

We expect a 15.0% loss to follow-up over 1 year in aim 2. Starting with n=240 will yield an effective sample size of 204 individuals in total, or 102 in each group, available for analysis in aim 2. A total estimate of n=200 will be enough to detect an average increase in the viral suppression proportion over the 3 follow-up visits of 16.0% from 24.0% assumed in the control arm to 40.0% in the coached-based MEI arm (odds ratio, OR 2.03), assuming a power of 85.0%. We expect a slightly greater loss to follow-up (20.0% loss to follow-up) in participants in aim 3. Starting with n=225 will yield an effective sample size of 180 individuals in total or 90 in each group. We estimate that a total of 180 participants (90 per group), and assuming a 15.0% average rate on PrEP in the control arm, we can detect an average increase of 14.0% to 29.0% (OR 2.31) with power 85.0%. Lost to follow-up estimates are based on the team’s prior work with this population.

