The success of the randomization process is measured by comparing the distribution of participant characteristics between the 2 groups at baseline. If the randomization process does not result in comparable groups, adjustment is made for group differences in the multivariable models. For aim 2, logistic regression is used to examine whether participants who receive MEI coach are more likely to be virally suppressed as well as retained and engaged in HIV care than participants in the SOC arm. Generalized estimating equations (GEE) are used to determine whether treatment assignment predicts differences in retention for the coached-based MEI versus the SOC groups using repeated measurements over a 12-month period. GEE is used for the longitudinal data as it adjusts for the intra-personal correlation of repeated measurements on the same individual and provides an estimate of the standard error that is robust to misspecification of this correlation structure.

For aim 3, to evaluate whether YBLMSM and YBLTW receiving coached-based MEI have greater uptake of PrEP over 12-months, a survival model is used to examine whether intervention assignment is associated with time to PrEP use. GEE is used to determine whether treatment assignment predicts differences in PrEP utilization and adherence over time for the coached-based MEI versus SOC groups using the repeated measures over the 12-month period [91]. For both aims, we explore trends in uptake and adherence to treatment or PrEP for the intervention group compared with the control group by including an interaction term between time from randomization and treatment assignment.

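### Participants are randomized individually but the MEI is delivered through coaches; the stated models and the 85% power in both trials allow for no difference between coaches.

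*Protocol article*

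**What the plan says.** Both trials randomize individuals 1:1, in rounds of four, stratified by site and age group (Study Procedures for aims 2 and 3; Data Collection for Aims 2 and 3). Coach is not a stratification factor.

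The MEI is then delivered by trained coaches, each with assigned participants. Under Study Intervention (aim 2), "the MEI coach develops an individually tailored plan", and "The MEI coach will determine the participant’s desire for support, and the frequency and schedule of messages". The section on the MEI coach intervention for aim 3 describes the same approach. The number of coaches, their caseload, and whether the same people coach in both trials are not given.

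Data Analysis assigns these models:

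- Aim 2, suppression (primary): logistic regression, no clustering term stated.
- Aim 2, retention (secondary): GEE over repeated measurements.
- Aim 3, PrEP uptake: a survival model, no frailty or clustered variance stated; PrEP use and adherence over time: GEE.
- CRAFFT scores: models adjusting for correlation within a person.

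The reason given for GEE is that "it adjusts for the intra-personal correlation of repeated measurements on the same individual". The robust standard error is offered as protection against misspecifying that same within-person structure.

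Sample Size Considerations plans aim 2 for a rise "from 24.0% assumed in the control arm to 40.0% in the coached-based MEI arm (odds ratio, OR 2.03), assuming a power of 85.0" percent. For aim 3 it states that "we can detect an average increase of 14.0% to 29.0% (OR 2.31) with power 85.0" percent. Neither calculation mentions coaches.

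**The concern.** When one arm is treated through providers who each see several participants, the outcomes of people sharing a provider can be correlated even though individuals were randomized. This is a partially nested design. That each coach serves several participants is an inference, but a fair one at about 100 MEI participants per trial.

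A variance computed as if MEI participants were independent leaves the between-coach part out. A robust standard error clustered on the person does not recover it, because the missing correlation lies between persons. The trials' central claim is that a coach program works. If coaches differ, part of what a few strong or weak coaches achieve would be read as the effect of the program, with more precision than the data support.

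**Working it through.** **Inputs from Sample Size Considerations.** Aim 2: 100 per arm, 24% vs 40%, averaged over 3 follow-up visits. Aim 3: 90 per arm, 15% vs 29%. Power 85% in each.

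**Assumed, because not stated.** Two-sided 5% test; 3 visits in aim 3 too; k = 3 to 8 coaches per trial with equal caseloads; coach ICC 0.01 to 0.05; no clustering in SOC; normal approximation.

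**Step 1: the plan's own figures.** The attrition arithmetic is right: 240 × 0.85 = 204 and 225 × 0.80 = 180. A two-proportion test has

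power = Φ{[Δ − 1.96√(2p̄q̄/n)] / √[(p₁q₁ + p₂q₂)/n]}.

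At a single visit this gives 68% (aim 2) and 62% (aim 3). Averaging 3 visits with within-person correlation ρ replaces n by n/w, where w = (1 + 2ρ)/3. Power of 85% is then reached at ρ ≈ 0.49 (w = 0.662) in aim 2 and ρ ≈ 0.37 (w = 0.578) in aim 3. Neither ρ nor alpha is stated, so 85% is attainable but not confirmable. It serves here as the baseline, and no coach term is needed to reach it. (Separately, 24% vs 40% is an odds ratio of 2.11, not 2.03; nothing below depends on that.)

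**Step 2: add between-coach variance in the MEI arm.** Let e = ICC × (1/k − 1/n). Then

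- V₀ = p̄q̄(2w/n + e)
- V₁ = p₁q₁w/n + p₂q₂(w/n + e)
- power of a valid test = Φ[(Δ − 1.96√V₀)/√V₁]
- type I error of the unadjusted test = 2{1 − Φ[1.96/√(1 + e·n/(2w))]}

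Example: aim 2, k = 4, ICC 0.05.

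- e = 0.05 × (0.25 − 0.01) = 0.012 and w/n = 0.00662.
- √V₀ = √[0.2176 × (0.01324 + 0.012)] = 0.0741.
- √V₁ = √[0.1824 × 0.00662 + 0.24 × 0.01862] = 0.0753, against 0.0529 without the coach term (ratio 1.42).
- Power = Φ[(0.16 − 0.1452)/0.0753] = 58%.
- Type I error = 2{1 − Φ(1.96/√1.906)} = 16%.

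Power, with type I error of the unadjusted test in brackets:

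| Trial, coaches | ICC 0.01 | ICC 0.02 | ICC 0.05 |
|---|---|---|---|
| Aim 2, k = 3 | 76% (8%) | 68% (11%) | 52% (19%) |
| Aim 2, k = 4 | 78% (7%) | 72% (9%) | 58% (16%) |
| Aim 2, k = 8 | 82% (6%) | 79% (7%) | 70% (10%) |
| Aim 3, k = 3 | 76% (8%) | 68% (11%) | 51% (19%) |
| Aim 3, k = 4 | 78% (7%) | 72% (9%) | 57% (16%) |
| Aim 3, k = 8 | 82% (6%) | 78% (7%) | 70% (10%) |

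At ICC 0 every cell returns to 85% (5%).

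**Step 3: dependence on the ICC scale.** Step 2 puts the ICC on the single-visit variance. On the person-average outcome, the MEI design effect is DE = 1 + (m − 1) × ICC with m participants per coach. In aim 2 with 102 per arm, k = 4 and ICC 0.05:

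- m = 25.5 and DE = 2.23.
- Null variance inflation = (1 + 2.23)/2 = 1.61, so type I error is 12%.
- Inflation under the alternative = (0.1824 + 0.24 × 2.23)/0.4224 = 1.70, so power = Φ(2.996/√1.70 − 1.96) = 63%.

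Aim 3 (m = 22.5, DE = 2.08) gives 11% and 64%. The direction is the same and the size milder.

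**Step 4: enrollment reported so far** (k = 4, ICC 0.05, person-average scale, equal split). Aim 2: 36 enrolled, 18 in MEI, m = 4.5, DE = 1.18, type I error about 6%. Aim 3: 123 enrolled, m ≈ 15.4, DE = 1.72, about 9%.

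**The case against.** The strongest reply is that this is a condensed article. It never says that coach variation will be ignored, its sentence about GEE is correct, and random-effect structure is often left to the full protocol or SAP. Sample Size Considerations also omits alpha and the within-person correlation, so it is plainly abbreviated. This lowers the weight of the point but does not remove it: the article names its models and makes a numerical power claim, and followed as written these contain no between-coach variance.

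Four stronger readings are tempting but not supported:

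- *That a small pool of coaches is shared by both trials.* No number is given, and the article says only that the support infrastructure is duplicated for aim 3. The argument needs only several participants per coach within a trial.
- *That coaches are supervised because their delivery is known to vary.* The text does not say so. Common training, biweekly supervision and fidelity review would tend to make coaches alike and so lower the ICC. Contact frequency also depends on what participants want.
- *That the intervals are certainly too narrow and the false-positive rate certainly above 5%.* This requires coach ICC above 0 and inference beyond these coaches. If the MEI changed nothing for anyone, individual randomization would keep the test at its level; the inflated rates describe coaches whose effects differ but average zero.
- *That the within-person GEE correction governs the aim 2 primary outcome.* That GEE sentence concerns retention; suppression is assigned to logistic regression.

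Two objections to the remedy also stand. With one coach per site, coach cannot be separated from site within the MEI arm, and three or four clusters barely support a random effect. SOC participants also meet assigned personnel, so clustering may not be confined to MEI. Both argue against making a coach random effect the primary model.

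**Conclusion.** The point holds in conditional form. The models as stated address at most correlation within a person, and the 85% power in each trial assumes no between-coach variance. If coaches differ and the conclusion is about the MEI program rather than these particular coaches, the MEI-SOC standard errors are understated, by a factor of about 1.05 to 1.60 over the range tried. The matching type I error is about 6% to 19% and power about 51% to 82% at planned size.

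These figures are illustrations. They rest on an assumed 3 to 8 coaches, an assumed ICC of 0.01 to 0.05, its scale, equal caseloads and an 85% baseline that cannot be confirmed. At the enrollment reported so far the effect is slight in aim 2 and moderate in aim 3. The point is worth acting on because the remedy is cheap, but it does not show the planned primary analyses to be invalid.

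**What to change.** 1. **Sample Size Considerations.** State that the 85% in each trial assumes no between-coach variance. Give the actual number of coaches and caseload, and show power over a range of coach ICCs, naming the scale of the ICC.
2. **Data Analysis.** Keep the stated primary models. Carry coach identity into the analysis dataset; the contact log described under Fidelity should supply it. For each primary outcome add a sensitivity analysis that allows for coach clustering in the MEI arm (partially nested, with a small-sample correction), and report the coach ICC. Where coaches are too few, or coincide with site, report outcomes by coach instead and state that inference is conditional on these coaches.

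The cost is some wording and one extra analysis per primary outcome, with no new participants, visits or measurements. The price is wider intervals in the sensitivity analysis, a less favorable stated power, and an imprecise ICC if coaches are few.

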#### In-Depth Interviews

In-depth interviews are completed as part of routine follow-up visits (Table 2). Target enrollment for interviews is 6 participants (3 SOC and 3 MEI) per aim per site (total of 36). This total will be sufficient to reach informational redundancy across the 3 cities [53]. Interviews focus primarily on changes in self-reported sexual orientation and gender identity, mentorship and community experiences, health care navigation, barriers or facilitators to care or research, and substance use specific to YBLMSM and YBLTW. Initial analysis of the interview data follows the same procedure outlined in the formative data section.

Further analysis will allow for responses and interview themes to be compared across sites, time, participant’s age, and other sociodemographic characteristics. The findings are presented to the team on an ongoing basis to provide insight into barriers and facilitators of engagement and intervention experiences over time. Participants are paid US $25 for each interview.

#### Consent and Human Subjects Considerations

Participants in this study go through a verbal consent process (paper or electronic) to enter the formative research, RDS survey, and/or enroll in the RCTs. Electronic consent displays on the screen before the web-based survey. Participants are prompted to provide their signature on the screen as an acknowledgment of consent. This study has obtained a waiver of parental permission for unaccompanied participants and adolescents seeking confidential services who are aged 15 to 17 years under 45 CFR Part 46.408(c), which is in line with local laws in (Maryland HG Section 20-102), Pennsylvania law (IRB SOP 505; Minors’ Consent Act, 35, PS 10101), and Washington DC law (code 600.7). For youth aged 15 to 17 years recruited through RDS that are not seeking confidential services, we will use *advocates* (trained social workers) who are independent counselors to work with each participant aged 15 to 17 years before and during the informed consent to ensure adequate comprehension of risks and benefits of participating in the research in Baltimore.

To provide adolescents with additional protections, a certificate of confidentiality has been obtained from the National Institutes of Drug Abuse (NIDA). All staff are trained on confidentiality, HIPAA (Health Insurance Portability and Accountability Act) privacy protections, cultural competency, adolescent counseling techniques, pre- and posttest counseling, mandated reporting, statutory rape laws (specific to the local context), and managing situations of child or sexual abuse. Adolescents who describe physical or sexual abuse or express concerns about mental health are linked to child protective or social work services to ensure their safety. This study was approved by the CHOP, the Children’s National Hospital, and the Johns Hopkins School of Public Health institutional review boards.

## Results

A total of 585 participants have been screened to date, with 450 (76.9%) enrolled. Recruitment monitoring showed that seed propagation was slow and reached low depths, frequently ranging from 1 to 3 waves of recruitment before stopping.

Table 3 summarizes the key demographic characteristics and reported substance use of baseline participants (N=402) and those who enrolled in aim 2 (n=36) and aim 3 (n=123). In summary, the median age was 21.6 years at enrollment, most participants identify as African American/Black (76.6%), 41 (10.2%) identify as transgender or female, 145 (41.5%) completed high school, and 145 (36.1%) had at least some college or technical education. One-quarter (97/402, 24.1%) reported having been without a place to stay in the last year, and most participants reported a history of substance use: alcohol (77.6%); cannabis (76.6%); and about a fifth reported use of other drugs including opioids, amphetamine, and cocaine (21.9%). Almost a quarter (n=100) reported engaging in transactional sex for a place to stay, money, or food. Moreover, 10% of the participants described having been forced to do something sexually (coerced sex, n=40) and 10.8% (n=43) described being forced not to use a condom during sex. Qualitative research is also ongoing. A total of 19 baseline interviews have been conducted within the 3 sites, with 9 interviews from aim 2 participants and 10 interviews from aim 3 participants.

**Table 3 table3:** Demographic characteristics and substance use at baseline for participants.

Characteristics		AMSAB^a^ participants (N=402)	Participants in aim 2 (n=36)	Participants in aim 3 (n=123)
Age (years), median (IQR)		21.6 (19.3-23.5)	22.9 (19.8-23.9)	20.7 (18.8-22.8)
**Age category (years),** **n (%)**				
	15-17	42 (10.4)	4 (11.1)	17 (13.8)
	18-24s	360 (89.6)	32 (88.9)	106 (86.2)
**Race,** **n (%)**				
	Black/African American	308 (76.6)	30 (83.3)	91 (74.0)
	Black/mixed	28 (7.0)	1 (2.8)	6 (4.9)
	Latino/Black	26 (6.5)	3 (8.3)	12 (9.8)
	Hispanic	30 (7.5)	0 (0.0)	9 (7.3)
	Unknown	10 (2.5)	2 (5.6)	5 (4.1)
**Gender,** **n (%)**				
	Male	347 (86.3)	30 (83.3)	108 (87.8)
	Transgender	28 (7.0)	3 (8.3)	8 (6.5)
	Female	13 (3.2)	2 (5.6)	1 (0.8)
	Gender nonbinary or nonconforming	13 (3.3)	1 (2.8)	6 (4.8)
**Sexual identity,** **n (%)**				
	Gay	255 (63.4)	25 (69.4)	86 (69.9)
	Bisexual	88 (21.9)	5 (13.9)	24 (19.5)
	Heterosexual	25 (6.2)	1 (2.8)	5 (4.1)
	Queer	10 (2.5)	0 (0.0)	4 (3.2)
	Pansexual	9 (2.2)	2 (5.6)	2 (1.6)
	Other or questioning or missing	33 (3.2)	3 (8.3)	2 (1.6)
**Highest level of education,** **n (%)**				
	<High school	89 (22.1)	12 (33.3)	29 (23.6)
	High school graduate	167 (41.5)	13 (36.1)	50 (40.6)
	>High school	145 (36.1)	10 (27.8)	44 (35.8)
**Are you employed?,** **n (%)**				
	Yes	227 (56.5)	17 (47.2)	71 (57.7)
	No	174 (43.3)	18 (50.0)	52 (42.2)
**Been without a place to stay in the last 12 months,** **n (%)**				
	No	301 (74.9)	26 (72.2)	103 (83.7)
	Yes	97 (24.1)	9 (25.0)	20 (16.3)
**Substance use ever,** **n (%)**				
	Tobacco	154 (38.3)	26 (72.2)	35 (28.5)
	Alcohol	312 (77.6)	29 (80.6)	97 (78.9)
	Cannabis	308 (76.6)	30 (83.3)	100 (81.3)
	Any other drugs (amphetamine, cocaine, opioids, sedatives, or inhalants)	88 (21.9)	15 (41.7)	27 (22.0)

^a^AMSAB: assigned male sex at birth.

## Discussion

### Principal Findings

The lack of data focused on identifying, recruiting, and engaging YBLMSM and YBLTW who are living with or at risk of acquiring HIV and have high rates of substance use contribute to health disparities and a public health crisis in this population.

Previous studies have described the use of RDS as an effective strategy to reach hard-to-reach populations. Some have also demonstrated challenges (eg, slow propagation) in reaching YBLMSM and YBLTW, though these studies have failed to examine different seed selection methods used in RDS [94]. The PUSH study allows us to examine assumptions about RDS seed selection methods and barriers to participating in research, which may help to inform future recruitment and sampling methods for interventions with sexual and gender minority youth.

This intervention study collects critical data on whether modification of an existing model for persons living with HIV can be used for YBLMSM and YBLTW living with HIV and those at risk for HIV. Evaluation of the PUSH study will address multiple gaps, including what components (eg, mobile app, telephone, and coach support) are needed to improve youth-based interventions to be more accessible and able to simultaneously address HIV treatment or prevention and substance use care. Although peer support is thought to be an additional strategy to improve access to care in this population [95-97], the gap in existing knowledge about the impact of coaches and/or peer-based strategies leaves prevention and treatment programs uncertain about their efficacy and effectiveness.

